## Abstract

**Background:**

Minimally invasive direct coronary artery bypass (MIDCAB) surgery offers an effective option for coronary artery disease (CAD) patients with the avoidance of median sternotomy and fast postoperative recovery. However, MIDCAB is still associated with significant postoperative pain which may lead to delayed recovery. The erector spinae plane block (ESPB) is a superficial fascial plane block. There have not been randomized controlled trials evaluating the effects of ESPB on analgesia and patient recovery following MIDCAB surgery. We therefore designed a double-blind prospective randomized placebo-controlled trial, aiming to prove the hypothesis that ESPB reduces postoperative pain scores in patients undergoing MIDCAB surgery.

**Methods:**

The study protocol has been reviewed and approved by the Ethical Review Committee of Peking University People’s Hospital. Sixty adult patients of either sex scheduled for MIDCAB surgery under general anesthesia (GA) will be included. Patients will be randomly allocated to receive either a preoperative single-shot ESPB with 30 mL of ropivacaine 0.5% (ESPB group) or normal saline 0.9% (control group). The primary outcomes are the difference between the two groups in numeric rating scale (NRS) scores at rest at different time points (6, 12, 18, 24, 48 h) after surgery. The secondary outcomes include NRS scores on deep inspiration within 48 h, postoperative hydromorphone consumption, and quality of patient recovery at 24 h and 48 h, using the Quality of Recovery-15 (QoR-15) scale. The other outcomes include intraoperative fentanyl requirements, the need for additional postoperative rescue analgesics, time to tracheal extubation and chest tube removal after surgery, incidence of postoperative nausea and vomiting (PONV) and postoperative cognitive dysfunction (POCD), intensive care unit (ICU) length of stay (LOS), hospital discharge time, and 30-day mortality. Adverse events will be also evaluated.

**Discussion:**

This is a novel randomized controlled study evaluating a preoperative ultrasound-guided single-shot unilateral ESPB on analgesia and quality of patient recovery in MIDCAB surgery. The results of this study will characterize the degree of acute postoperative pain and clinical outcomes following MIDCAB. Our study may help optimizing analgesia regimen selection and improving patient comfort in this specific population.

**Trial registration:**

The study was prospectively registered with the Chinese Clinical Trial Registry (trial identifier: ChiCTR2100052810). Date of registration: November 5, 2021.

## Introduction

### Background and rationale {6a}

Over the past 10 years, minimally invasive direct coronary artery bypass (MIDCAB) surgery has been gaining popularity with smaller skin incisions and surgical trauma than conventional sternotomy coronary artery bypass grafting (CABG) [1]. The MIDCAB provides an effective alternative to coronary artery disease (CAD) patients requiring single or multi-vessel CABG through left anterior thoracotomy between the ribs [2]. It does not increase the risk of perioperative adverse cardiovascular and cerebrovascular events or 30-day mortality with reduced postoperative pain, faster recovery, and improved quality of life [3, 4]. However, MIDCAB surgery still causes moderate to severe postoperative pain that is related to thoracotomy, intercostal retraction, and chest drainage tubes.

Poorly controlled acute pain may lead to increased cardiopulmonary complications, delayed recovery, and prolonged intensive care unit (ICU) and hospital length of stay (LOS) as well as higher risk of developing chronic pain [5]. Therefore, the optimum method for postoperative analgesia is of critical importance in patients undergoing MIDCAB.

Postoperative pain management in cardiac surgery has traditionally been based on high-dose systemic opioids, which are effective but also responsible for kinds of feared effects including respiratory depression, nausea and vomiting, urinary retention, or constipation [6]. Regional anesthesia techniques are key components of multimodal analgesia in a variety of surgical settings. Thoracic epidural analgesia (TEA) and paravertebral block (PVB) have been applied as standard regional analgesia for thoracotomy. However, the use of these blocks in cardiac surgery has been controversial with consideration of the possible hemodynamic instability due to extensive sympathetic block. Moreover, intraoperative heparinization and perioperative antiplatelet therapy may result in an increased risk of serious block-related complications such as epidural or paravertebral hematoma. As a potential alternative, ultrasound-guided interfascial plane blocks have become increasingly popular as they are considered to be safer for cardiac surgeries with easier techniques to perform than TEA and PVB [7].

Erector spinae plane block (ESPB) is a superficial musculofascial plane block that injects local anesthetics into the space between the erector spinae muscles (ESM) and the transverse processes (TP) [8]. The efficacy of ESPB has been proven in thoracic and breast surgeries [9, 10]. In cardiac surgeries, 1 before-and-after study and 1 retrospective case–control study were conducted in adult cardiac patients using ESPB as a technique to manage acute postoperative pain [11, 12]. Only three randomized controlled trials of bilateral ESPB on postoperative analgesia for open cardiac surgery have been reported [13–15]. Besides, ESPB has also been shown to provide effective analgesia for mini-thoracotomy valve replacement surgery and left ventricular assist device implantation in observational studies and case series [16–18].

However, to our knowledge, no randomized controlled trials have evaluated this block in terms of analgesic effects or short-term and long-term outcomes among patients undergoing MIDCAB surgery. Here, we describe a double-blind prospective randomized placebo-controlled study, aiming to evaluate the effects of a preoperative unilateral ultrasound-guided single-shot ESPB on analgesia and quality of recovery among MIDCAB patients.

### Objectives {7}

The primary goal of this study is to evaluate the efficacy of preoperative single-shot ESPB on postoperative analgesia within 48 h compared with placebo after MIDCAB surgery.

Our secondary goals are to investigate whether the use of ESPB:Promotes quality of patient recovery;Reduces intraoperative opioids requirements and postoperative analgesic needs;Facilitates early extubation and chest tube removal;Shortens ICU stay and hospital discharge time; andDecreases 30-day mortality.

### Trial design {8}

We are conducting a single-center, parallel-group, randomized controlled exploratory trial, with a 1:1 allocation of participants randomized to the intervention and control groups.

## Methods: participants, interventions, and outcomes

### Study setting {9}

The study site is Peking University People’s Hospital, a university-affiliated teaching hospital in Beijing, China.

### Eligibility criteria {10}

The inclusion criteria are as follows: adult patients from 18 to 75 years of either sex will be scheduled for elective MIDCAB surgery under general anesthesia (GA). The exclusion criteria are as follows: New York Heart Association (NYHA) grading IV, preoperative ejection fraction (EF) < 40%, body mass index (BMI) < 18 or > 35, redo or emergency surgery, coagulopathy, localized infection at the block site, allergy or intolerance to local anesthetics, hepatic or renal insufficiency, diagnosed mental disorder, history of chronic pain conditions requiring opioid usage, and patient refusal.

### Who will take informed consent? {26a}

The principal investigator will assess eligible patients to participate in this study based on the inclusion and exclusion criteria. The research team members will introduce the study protocol to the participants. If the patient is willing to participate in this study, a written informed consent will be given for the patient’s signature.

### Additional consent provisions for collection and use of participant data and biological specimens {26b}

Not applicable. No biological specimens of the participant will be collected during the trial.

## Interventions

### Explanation for the choice of comparators {6b}

The novel ESPB has to be evaluated for analgesic efficacy in MIDCAB surgery. The choice of interventions will help us to achieve valuable information for a better understanding of the impact of this regional technique on pain control. The intravenous (IV) patient-controlled analgesia (PCA) and rescue analgesics will serve as standard postoperative analgesia and prevent therapeutic gaps in case of ineffective block.

## Intervention description {11a}

### Standard perioperative management

All patients will receive GA for MIDCAB surgery. A radial arterial catheter will be inserted for continuous invasive blood pressure (IBP) monitoring. Induction of GA will be a combination of IV midazolam (0.03–0.05 mg/kg), etomidate (0.15–0.2 mg/kg), fentanyl (3–5 μg/kg), and cis-atracurium (0.15–0.2 mg/kg), and then an appropriate sized left-sided double-lumen tube will be inserted. Mechanical ventilation will be performed in volume control mode. The respiratory frequency will be adjusted to achieve end tidal carbon dioxide (ETCO_2_) between 30 and 35 mmHg. A 7-Fr triple-lumen central venous catheter will be placed after induction under ultrasound guidance to monitor central venous pressure (CVP). Continuous infusion of propofol (3–5 mg/kg), cis-atracurium (0.1–0.2 mg/kg/h), and dexmedetomidine (0.5–0.8 μg/kg/h) will be used for anesthesia maintenance with additional fentanyl boluses according to bispectral index (BIS) value and hemodynamic status.

During the surgical procedure, the BIS value will be kept between 40 and 60 and IBP within ± 20% of the baseline value. In case of hypertension (defined as IBP > 20% of baseline value), the attending anesthesiologist will check the anesthesia depth and volume status of the patient, then increase propofol infusion rate by 1 mg/kg and/or administer fentanyl bolus by 1 μg/kg or nicardipine 0.1–0.3 mg. Hypotension (IBP < 20% of baseline value) will be corrected by decreasing propofol by 1 mg/kg and/or fluid volume loading by 3 mL/kg. Continuous infusion of phenylephrine (0.3 μg/kg/min) or dopamine (3 μg/kg/min) will be initiated if normal IBP is still not achieved. Tachycardia (heart rate > 80 bpm) will be treated with esmolol bolus by 0.5 mg/kg, while bradycardia (heart rate < 45 bpm) will be treated with anisodamine by 1–3 mg, respectively. Intraoperative patient nasopharyngeal and urinary bladder temperature as well as urine output will also be monitored.

PCA with IV hydromorphone will be prescribed for all patients with no basal infusion and an intermittent bolus dose of 0.2 mg, with a lock-out period of 10 min. IV tropisetron 5 mg will be used at the end of surgery for postoperative nausea and vomiting (PONV) prophylaxis.

All IV anesthetic infusions including sedatives and analgesics will be stopped upon completion of surgery; afterwards, the patients will be transferred to the cardiac ICU whereby postoperative hemodynamic and respiratory parameters are evaluated. No sedatives or analgesic infusions will be administered in the cardiac ICU until the patient is extubated. Patients will be extubated when the following weaning criteria are met: patients are conscious with spontaneous breath in pressure support (PS) mode of 6–8 cmH_2_O and FiO_2_ < 0.4, respiratory rate between 12 and 20 breaths/min, PaO_2_ ≥ 60 mmHg, PaCO_2_ ≤ 45 mmHg, no need for inotrope use to maintain mean arterial pressure (MAP) ≥ 60 mmHg, urine output > 0.5 mL/kg/h, no signs of active bleeding, and the amount of drainage from chest tube reaching to 50 mL/h.

If the patient required, extra bolus of hydromorphone 0.4 mg (up to 1.2 mg per hour) will be delivered via PCA device. IV fentanyl 50 μg will be used for rescue analgesia in case the numeric rating scale (NRS) score at rest is still equal or greater than 4 or the patient demands additional analgesia. No any other specific protocol will be used by the cardiac ICU staff to manage analgesia after surgery. Forty-eight hours postoperatively, PCA will be discontinued and data will be transmitted from the pump to the institutional analgesia database. After being transferred to the ward, further analgesic treatment with oxycodone and acetaminophen will be prescribed for the patient if necessary.

### Criteria for discontinuing or modifying allocated interventions {11b}

Discontinuation criteria are as follows: surgery is converted to median sternotomy, patients who undergo redo surgery before hospital discharge, patients who are unconscious or unable to cooperate at the time points of postoperative follow-up, and patients who decide to leave the study. The patient has the right to withdraw the informed consent and cease participation in the study at any time. Participants who leave early will be provided with local standard of care for MIDCAB surgery.

### Strategies to improve adherence to interventions {11c}

Prior to the start of the study, cardiac anesthesiologists in charge of the surgery will receive information about the study protocol and will be trained in the handling of perioperative management, which will improve protocol adherence. Apart from the intervention, the participants will receive standard care during hospital admission.

The investigators will make best effort to do a close follow-up and good communication with the participants throughout the study period. The participants will be provided with detailed study timeline before data collection and forenotice of the upcoming follow-up visit. Any question or concern related to the study and clinical treatment from the participants will be responded patiently in detail.

### Relevant concomitant care permitted or prohibited during the trial {11d}

Any interventions or concomitant care that may influence the study outcomes are prohibited, such as other type of regional blocks.

### Provisions for post-trial care {30}

The single-shot ESPB is a relatively safe technique with no block-related complications that has been reported in meta-analyses [19, 20]. Thus, the participants are not expected to suffer injury from participating in the trial. If any harm was occurred, the patient will be treated by appropriate departments in our hospital.

### Outcomes {12}

The primary outcome is pain intensity measured by the NRS score at rest at different time points (6, 12, 18, 24, 48 h) after MIDCAB. The NRS is a self-reported 11-point scale representing different degrees of pain. The number 0 represents painless, while 10 represents worst pain ever. The intensity of pain can be categorized into mild (1 to 3), moderate (4 to 6), and severe (7 to 10). The secondary outcomes are NRS scores on deep inspiration within 48 h after surgery, postoperative 48 h hydromorphone consumption, and quality of patient recovery at 24 h and 48 h, assessed by the Quality of Recovery-15 (QoR-15) scale. Other outcomes include intraoperative fentanyl requirements, additional use of postoperative rescue analgesics, time to tracheal extubation and chest tube removal after surgery, LOS in ICU, and hospital discharge time. Adverse events including PONV, postoperative cognitive dysfunction (POCD), atrial fibrillation, pleural effusion, pericarditis, and block-related complications, for instance, hematoma, pneumothorax, and infection, will be recorded. Thirty-day mortality will also be evaluated as a safety outcome.

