## Statistical methods

### Statistical methods for primary and secondary outcomes {20a}

Statistical analysis will be done using SPSS Statistics (IBM: V. 24). Before analysis, the normality of the data distribution will be assessed using the Shapiro–Wilk test and Q–Q plots. For postoperative NRS scores, we will use repeated measurement with post hoc testing. For the other outcomes, postoperative hydromorphone consumption, QoR-15 scale, intraoperative fentanyl requirements, time to tracheal extubation and chest tube removal after surgery, LOS in ICU, and hospital discharge time will be analyzed with the independent samples *t* test or Mann–Whitney *U* test. The incidence of PONV, POCD, additional use of postoperative rescue analgesics, and 30-day mortality will be compared by the *χ*^2^ or Fisher’s exact test when necessary. All *P* values will be two sided, and statistical differences will be defined as less than 0.05. Missing data will be handled with multiple imputation methods.

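### The only postoperative opioid amount analysed is 48 h hydromorphone; rescue fentanyl in the same window counts only as yes/no, so opioid sparing may be understated

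*Protocol article*

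**What the plan says.** Outcomes {12} lists "postoperative 48 h hydromorphone consumption" as a secondary outcome. Further down, among the other outcomes, it lists "additional use of postoperative rescue analgesics", with no dose attached.

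Standard perioperative management (under Intervention description {11a}) gives all patients hydromorphone PCA and allows extra hydromorphone boluses through the same device. Beyond that, "IV fentanyl 50 μg will be used for rescue analgesia" when the "score at rest is still equal or greater than 4 or the patient demands additional analgesia". At 48 h "PCA will be discontinued and data will be transmitted from the pump to the institutional analgesia database". The section then says that, after transfer to the ward, "further analgesic treatment with oxycodone and acetaminophen will be prescribed for the patient if necessary".

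Statistical methods {20a} assigns hydromorphone consumption a t test or Mann–Whitney U test. Rescue is handled differently: "The incidence of PONV, POCD, additional use of postoperative rescue analgesics, and 30-day mortality will be compared by the" chi-square or Fisher's exact test.

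Objectives {7} sets a wider aim than one drug, namely whether the block lowers the need for analgesics after surgery. Plans for assessment {18a} says that analgesic consumption is collected at 24 h and 48 h, without naming the drugs.

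**The concern.** A patient's opioid intake in the first 48 hours can come from two drugs, but the plan quantifies only one. The uncounted drug is not given at random. Its trigger is a threshold on resting pain, which is the primary outcome, or the patient's request. If the block changes resting pain, it should also change how often fentanyl is given. The hydromorphone total therefore omits most in the arm with more rescue, and the yes/no comparison does not recover the amount.

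What is at stake is the reading of a secondary outcome. A real reduction in opioid use could look smaller than it is, or be missed, and the objective on analgesic need would be only partly answered.

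**Working it through.** The plan states no expected opioid consumption, so there is no figure of its own to reproduce. Its sample size concerns the pain score and does not bear on this point.

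**1. What is counted, and how (protocol article)**

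| Postoperative opioid | Within 48 h? | Amount analysed? |
|---|---|---|
| Hydromorphone, PCA demands (0.2 mg, 10 min lock-out) | Yes | Yes |
| Hydromorphone, extra 0.4 mg boluses through the PCA device | Yes | Yes |
| Fentanyl 50 μg rescue | Can be | No; incidence only |
| Oxycodone on the ward | Uncertain | No |

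Table 1 agrees: hydromorphone consumption is marked at 24 h and 48 h, and fentanyl requirements only at completion of surgery. Intraoperative fentanyl is a separate outcome.

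**2. Direction**

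Let H be mean hydromorphone (mg), R the mean number of 50 μg rescue doses, and c the hydromorphone-equivalent (mg) of one such dose. Leaving oxycodone aside, total opioid is T = H + cR. Taking control minus ESPB, with d the extra mean rescue doses in control:

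ΔH = ΔT − c × d

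If d > 0, the hydromorphone difference is smaller than the total difference by c × d. If d = 0, there is no distortion.

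**3. Size under assumptions**

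The protocol gives neither c nor d. Assume c = 0.25 to 1.0 mg and d = 0.5 to 2 doses. The uncounted difference c × d, in mg per patient, is:

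| c (mg) | d = 0.5 | d = 1 | d = 2 |
|---|---|---|---|
| 0.25 | 0.125 | 0.25 | 0.5 |
| 0.5 | 0.25 | 0.5 | 1.0 |
| 0.75 | 0.375 | 0.75 | 1.5 |
| 1.0 | 0.5 | 1.0 | 2.0 |

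Divided by the 0.2 mg PCA bolus, the range is 0.125 / 0.2 ≈ 0.6 to 2.0 / 0.2 = 10 boluses.

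**4. What that could do to a test (illustration only)**

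Take 30 patients per arm (60 at 1:1), an assumed true total difference of 3 mg and an assumed SD of 3.5 mg, held fixed. The standard error is 3.5 × √(2/30) ≈ 0.904 mg. With the normal approximation, power = Φ(difference / 0.904 − 1.96):

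- nothing uncounted: 3 / 0.904 − 1.96 ≈ 1.36, power 91%
- 0.5 mg uncounted: 2.5 / 0.904 − 1.96 ≈ 0.81, power 79%
- 1 mg uncounted: 2 / 0.904 − 1.96 ≈ 0.25, power 60%
- 2 mg uncounted: 1 / 0.904 − 1.96 ≈ −0.85, power 20%

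The 3 mg and 3.5 mg are not in the protocol; other values give other losses.

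**The case against.** The case against has real weight.

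- **Rescue is not ignored.** It is a named outcome with its own test, and the hydromorphone outcome is labelled as what it is. Read together, the two serve the objective in part. This stands, so it would be wrong to say that the objective goes unanswered. But incidence shows that arms differ in rescue, not by how much opioid.
- **The first escalation step is counted.** Extra hydromorphone boluses run through the PCA device, so part of any excess need in control will appear in the hydromorphone total. This stands. Only what goes to fentanyl is lost.
- **A reader might infer that patients are switched from hydromorphone to fentanyl or oxycodone.** The text does not support this. PCA is prescribed for all patients and stops at 48 h; fentanyl is added to it.
- **A reader might also infer that sparing could be overstated, if ESPB patients reach the ward sooner and move to oxycodone.** This is not established. Oxycodone is described after the 48 h PCA stop, so some or all of it may fall outside the window. The QoR-15, due at 24 h and 48 h, is completed on the ward, which suggests transfer before 48 h, but not that oxycodone is given while PCA runs.
- **The error works against the trial's own hypothesis if control needs more rescue**, on a secondary outcome in a trial that Trial design {8} calls exploratory. This limits the gravity. It does not make the estimate right.
- **Conversion tables usually belong in an analysis plan.** True, and their absence is not the criticism. The protocol itself fixes a single-drug outcome and a yes/no analysis of rescue.

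**Conclusion.** The point holds for rescue fentanyl. The plan as written leaves a pain-triggered opioid out of its only postoperative opioid amount and reduces that opioid to yes/no. If control patients need more rescue, opioid sparing is understated.

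The size cannot be known from the protocol. The range of about 0.1 to 2 mg hydromorphone-equivalent per patient rests wholly on the assumed conversion and rescue imbalance, and at its lower end it is less than one PCA bolus. Bias in both directions is not shown, and oxycodone is at most a possible addition. The primary outcome is untouched. This is a worthwhile, inexpensive improvement to a secondary outcome, not a flaw that threatens the trial's main conclusion.

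**What to change.** Before unblinding, define the secondary outcome as total postoperative opioid over 0–48 h in opioid equivalents. It should sum PCA and extra-bolus hydromorphone, rescue fentanyl, and any oxycodone given within the 48 h. Acetaminophen is not an opioid and stays out.

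- Fix the conversion factors in advance and repeat the analysis over a stated range of them.
- Keep hydromorphone alone as a supportive analysis, with the tests already planned.
- Report the rescue fentanyl dose per arm beside the incidence.

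The cost is small. Analgesic consumption is already collected at 24 h and 48 h; confirm that the case report form records each rescue drug with dose and time. The downside is that a conversion table must be chosen and brings some conversion error, which the sensitivity range makes visible. No change to treatment is needed.
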